## Abstract

**Background:**

Among youth living with HIV (YLH) aged 12-24 years who have health care in the United States, only 30% to 40% are virally suppressed. YLH must achieve viral suppression in order to reduce the probability of infecting others as well as increasing the length and quality of their own life.

**Objective:**

This randomized controlled trial aimed to evaluate the efficacy of an Enhanced Standard Care condition (n=110) compared to an Enhanced Stepped Care intervention condition (n=110) to increase viral suppression among YLH aged 12-24 years with established infection (not acutely infected).

**Methods:**

YLH (N=220) who are not virally suppressed will be identified at homeless shelters, health clinics, and gay-identified community-based organizations in Los Angeles, CA, and New Orleans, LA. Informed consent will be obtained from all participants. YLH will be randomly assigned to one of two study conditions: Enhanced Standard Care, which includes standard clinical care plus an automated messaging and monitoring intervention (AMMI), or an Enhanced Stepped Care, which includes three levels of intervention (AMMI, Peer Support via social media plus AMMI, or Coaching plus Peer Support and AMMI). The primary outcome is viral suppression of HIV, and YLH will be assessed at 4-month intervals for 24 months. For the Enhanced Stepped Care intervention group, those who do not achieve viral suppression (via blood draw, viral load<200 copies/mL) at any 4-month assessment will “step up” to the next level of intervention. Secondary outcomes will be retention in care, antiretroviral therapy adherence, alcohol use, substance use, sexual behavior, and mental health symptoms.

**Results:**

Recruitment for this study began in June 2017 and is ongoing. We estimate data collection to be completed by the end of 2020.

**Conclusions:**

This is the first known application of an Enhanced Stepped Care intervention model for YLH. By providing the lowest level of intervention needed to achieve viral suppression, this model has the potential to be a cost-effective method of helping YLH achieve viral suppression and improve their quality of life.

**Trial Registration:**

ClinicalTrials.gov NCT03109431; https://clinicaltrials.gov/ct2/show/NCT03109431

**International Registered Report Identifier (IRRID):**

DERR1-10.2196/10791

## Introduction

### Background

New diagnoses of HIV among youth aged 12-24 years continue to be a challenging public health problem in the United States [1,2], with one in four new HIV diagnoses and 60,900 youth living with HIV (YLH) [3]. The substantial improvements in scientists’ ability to prevent and treat HIV infection [4,5] are underutilized by YLH. Similar to adults, if a YLH has an undetectable viral load, there is a 94% likelihood of not transmitting HIV [6] and the YLH is likely to live longer [7] and have a better quality of life [8]. Furthermore, only 30% to 44% of those diagnosed are virally suppressed [2,9]. This study evaluates a Stepped Care model to support YLH to achieve viral suppression.

YLH are concentrated in areas of the United States where the epidemic has grown, with certain groups disproportionately impacted, particularly in the South [10]. Black and Latino men-who-have-sex-with-men are at the highest risk for new HIV infections [11]. Among youth diagnosed with HIV, 81% are gay, bisexual, and transgender youths (GBTY), with the highest rates reported among black and Hispanic/Latino men [2]. GBTY coming of age today may not perceive the same risk of premature death, which characterized young men earlier in the epidemic when there were fewer treatment options.

It is imperative that YLH achieve viral suppression in order to reduce the probability of infecting others as well as increase the length and quality of their lives [7,8]. Among YLH, viral suppression requires linkage and retention in care as well as antiretroviral therapy (ART) adherence. As part of the HIV Treatment Continuum [12], YLH must overcome all barriers to seeking and receiving medical care and then adhere daily to their ART [1,13]. Historically, achieving an undetectable viral load required 95% ART adherence [14]. However, rates as low as 80% may lead to viral suppression [15]; at present, the pills are combined in regimens and ART is more robust. The duration of “drug holidays” (ie, days without medication) is at least as important as the number of pills taken as prescribed when monitoring adherence that aims to result in an undetectable viral load [16]. However, even with only an 80% adherence rate required for viral suppression and the typical regimen consisting of only one pill daily, YLH are far from meeting this target.

Retention in care and adherence to ART are related. Although 41% of YLH know their serostatus, only 62% receive medical care within 12 months of diagnosis [1]. Retention rates can be low, with only one in four YLH retained in care at 3 years after treatment initiation [17]. Among one sample of YLH (atypically, 72% women), initial ART adherence was 69%, but by 1 year, ART adherence was negligible, partly due to only a 30% retention in HIV care [18]. Young people are also more likely to dropout from care than middle-aged and older adults [13,19]. Existing studies suggest that few YLH remain in medical care more than a year, ensuring that ART treatment adherence will also be low [20-22].

### Barriers to Adherence Among Youth Living With HIV

In addition to connecting YLH to care, it is important to identify and address barriers to adherence. Others have suggested that targeting patient group characteristics to improve adherence may not be the answer, but instead, focusing on individual needs with the flexibility to address specific identified barriers may be helpful [23]. Barriers can be structural issues, and many of the challenges to adherence faced by YLH are interrelated. Drawing upon the work of Maslow [24], Barroso and colleagues assert that people living with HIV must first have their basic biological and physiological needs met to become adherent, including food and transportation, and there must be a focus on reducing stigma and addressing community-level barriers that contribute to disparities [25]. Psychological issues can be part of this complex problem, and even forgetting to take one’s medication can be due to the lack of a set routine or a more complex process that involves cognitive or behavioral struggles [26]. Shame as well as mental health problems and substance abuse may also contribute to delayed medication initiation and difficulties with adherence [27]. Thus, it is important that interventions targeting viral suppression have the flexibility to address multiple factors in the lives of YLH.

### Intervention Innovation of the Protocol: Stepped Care

Stepped Care is a strategy used in managing chronic diseases and mental health problems [28-30], but has only recently been applied to YLH in one trial [31]. Using a Stepped Care approach, providers implement the least intensive intervention needed to achieve the treatment goal and intensify the intervention until the treatment goal is achieved. With this Stepped Care framework, this study will implement a low-intensity intervention, followed by sequential introduction of more intense and comprehensive interventions. The interventions at the lowest levels require little individual tailoring and may be sufficient for some youth. However, for YLH who do not achieve viral suppression, a more individualized, tailored intervention will be implemented.

Mobile technologies saturate the lives of youth and young adults and offer an opportunity for a variety of interventions. HIV mobile health interventions are a growing area of interest and have been used as interventions for both self-management and medication adherence [32]. One intervention that may be beneficial for Stepped Care models for YLH is an automated messaging and monitoring intervention (AMMI). AMMI interventions using daily text messaging have been shown to be a useful method for medication reminders for HIV-infected individuals [33] and have demonstrated positive effects on medication adherence [34-40] and viral load [41]. We have demonstrated the efficacy of text messaging interventions with various high-risk groups in prior studies [42-46]. In this study, AMMI is based on promoting ART adherence by enhancing self-management of one’s care using the concepts of social cognitive theory [32,47,48]. Self-management or self-monitoring among persons living with HIV can include reflection, reinforcement of behaviors, and support of cues to action such as taking medications [49]. Peer support is another intervention that is well-suited for use in a Stepped Care model. Positive relationships are a major dimension related to retention in care and adherence to ART medications [50-53]. Relationships provide motivation to increase retention in care for a range of other chronic diseases (eg, diabetes, weight reduction, alcohol treatment, and mental health) [54-56]. Although peer support is a component of many evidence-based interventions, there are mixed findings in the meta-analyses conducted on peer support; some found a significant benefit [57,58] and others found a major benefit [59]. Reviews of peer support studies for persons living with HIV, which aimed at reducing stress [60], have found peer support to be a critical intervention component. In particular, adolescence is a developmental period wherein the influence of peers is crucial and has been consistently recognized as an important period from the 1980s [61] to the most recent Lancet reviews on adolescent health determinants [62].

Coaching interventions adapted for YLH are more intensive, individualized interventions that can be used in a Stepped Care model. The roots of coaching can be traced to sports, where a coach, typically working with a group of youths, is a leader who provides guidance, support, and direction. The earliest mention of coaching in the literature was in the 1970s in relation to assertiveness training [63] and later as a method for improving social skills among children [64] and helping families [65] and other types of groups. Since then, coaching has increased in popularity as an alternative to psychotherapy in the business world [66] and as an intervention for a variety of health professionals. Originally done face-to-face, most recently, this type of intervention, commonly known as “health coaching,” is also delivered electronically [67]. Coaching has been used as an intervention for chronic pain [68], weight loss [69], HIV medication adherence [70], and other health conditions. A recent review of coaching interventions found positive effects in most studies but highlighted the need for research to be more specific in describing coaching interventions including the types of behavior-change strategies used [71].

## Methods

### Overview of Methods and Aims

As outlined in Figure 1, we will conduct a randomized control trial (RCT) to evaluate the efficacy of an Enhanced Standard Care Intervention (n=110) as compared to an Enhanced Stepped Care Intervention Model (n=110) in order to significantly increase viral suppression among YLH in two cities, Los Angeles, CA, and New Orleans, LA (Trial Registration: ClinicalTrials.gov NCT03109431). This protocol is part of the U19 Research Program Grant that is funded by the Adolescent Medicine Trials Network for HIV/AIDS Interventions (ATN 148; 1U19HD089886).

The specific aims of this study are (1) to assess if Enhanced Standard Care or an Enhanced Stepped Care results in the primary outcome of more sustained viral suppression and improvements in secondary outcomes, (2) to test whether secondary outcomes such as mental health symptoms and drug use mediate the effect of the intervention on viral suppression over time, (3) and to conduct a cost-effectiveness analysis to weigh the benefit of intervention effects on primary and secondary outcomes against intervention implementation costs beyond costs incurred through the standard of care.

All procedures in this study have been approved by the Institutional Review Board of the University of California, Los Angeles, which serves as the single Institutional Review Board of Record for researchers at the collaborating institutions.

### Recruitment

In both New Orleans and Los Angeles, teams of predominantly bachelor’s degree–level interviewers aim to screen up to 1500 youths to recruit a cohort of 220 seropositive youths. A description of the study sites in Los Angeles and New Orleans can be found in Rotheram-Borus’ and colleagues’ article [12].

### Inclusion and Exclusion Criteria

The current inclusion criteria are age of 12-24 years, HIV-positive status, established HIV infection (not acutely infected), and ability to provide informed consent. Exclusion criteria include age under 12 years or above 24 years, HIV-negative status, acute infection with HIV, inability to understand the study procedures due to intoxication or cognitive difficulties (any youth who appears to be under the influence of alcohol or drugs will be unable to enroll in the study but invited to return at a later date), and inability to provide voluntary written informed consent.

### Recruitment Procedures

To identify eligible participants, youth in high-risk settings will be asked to complete a brief screening and rapid HIV test. All screenings are done face-to-face with a study team member from our Recruitment, Engagement, and Retention Center. Older youths (aged 15-24 years) will provide oral consent for the screening, and younger youths (aged 12-14 years) will provide written consent for the screening to ensure that they understand the screening process. Next, all youths aged 12-24 years whose judgment does not appear to be impaired from a disability or substance use will be asked to give written informed consent to complete the screening. Interviewers are trained to assess for problems with cognition, and additional screening questions will be asked if any concerns are identified. To qualify as “eligible” for recruitment, youths must test seropositive on a rapid HIV test and be virally unsuppressed. Based on these screening criteria, eligible youths will be invited to complete the voluntary informed consent (we have a waiver of parental consent for minors). YHL will be randomized to the intervention conditions via the CommCare system (see next section) after viral load results are obtained and entered, which typically takes several days.

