Following completion of the baseline assessment, participants will receive a US $50 cash incentive. Any study participant who tests positive for HIV or a sexually transmitted infection (STI) will be offered immediate access to treatment.

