### Description of the Intervention

As shown in Figure 1, the Enhanced Stepped Care condition has three levels of intervention: Level 1, Enhanced Standard Care plus AMMI; Level 2, online peer support via social media plus AMMI plus Enhanced Standard Care; and Level 3, coaching plus online peer support via social media and AMMI plus Enhanced Standard Care. If YLH fail to be virally suppressed (based on analyses of viral load in the blood stream at 4-month intervals), YLH in the Enhanced Stepped Care condition will be provided the next level of intervention in addition to the other levels of care to which they were previously assigned. Note that these interventions overlap with our team’s other study of HIV-negative youths and are also described in Swendeman et al [49]. To assess dose of the interventions, we will examine the number of responses to the AMMI surveys (Level 1), the number of peer support posts and logins (Level 2), and the number of coaching sessions (Level 3).

#### Level 1

Level 1 of the Enhanced Stepped Care model is Enhanced Care plus AMMI. As this is not a medication treatment study, YLH are treated in the community using best practices that are consistent with available treatment guidelines for providers. However, given that YLH have failed to achieve viral suppression with the existing services available to them, we are enhancing standard care by adding an additional component. Thus, Enhanced Care includes existing services received by YHL from health care providers and other agencies as well as daily text messages. Messages for this study focus on five areas: wellness, health care, medication reminders, drug use, and sexual health. We have tailored and adapted preexisting libraries of theoretically based text messages that have been found to be successful in other RCTs with similar populations [80-83], with messages tailored for two different groups—GBTY and non-GBTY. Messages include a focus on empowering YLH (ie, “Don't rely on other people, take your health seriously,” and “When you take your meds regularly, you’re in control”) as well as providing health-related facts (“Meds keep HIV in check” and “Syphilis can increase your viral load”). The goal of AMMI is to target the areas that can impact adherence to ART that will translate into increased rates of viral suppression.

#### Level 2

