#### Sample Size Calculations

Sample size calculations are estimated for our primary analysis, which is a comparison of the probability of viral suppression between Enhanced Stepped and Enhanced Standard Care conditions over five time points. The first follow-up is not included in the comparisons because we anticipate that it will take 6 months for improvements in viral suppression to be seen in the Enhanced Stepped Care condition. Based on our proposed sample size of 220 (n=110 in each condition), we anticipate 80% power for a two-sided test with a .05 alpha level to detect time-averaged percentage differences in viral suppression as small as 9%-13% between conditions. Based on consultation with HIV clinicians, we expect viral suppression rates to be fairly low in the Enhanced Standard Care condition, and we will use a range of rates from 6% to 20% in our calculations. Calculations assume a compound symmetry covariance structure. An autocorrelation coefficient is specified to account for correlations between repeated measurements. Calculations are conducted with a range of autocorrelation coefficient values similar to what we have found in prior studies, from .1 to .3. Lastly, we make a conservative assumption of 20% loss to follow-up so that the sample size in each condition is 88. In practice, we anticipate a much lower attrition rate. Sample size calculations were carried out using Power Analysis and Sample Size software, version 08.0.11 (Englewood, NJ) [106].

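### Eligibility admits newly diagnosed, never-treated youth, but the intervention rationale describes all entrants as having failed existing services, and the primary model adjusts for this status only if the arms happen to differ on it

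*Protocol article*

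**What the plan says.** All references are to the protocol article.

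- **Who may enter.** Recruitment Procedures state that "youths must test seropositive on a rapid HIV test and be virally unsuppressed". Inclusion and Exclusion Criteria add "established HIV infection (not acutely infected), and ability to provide informed consent", together with age 12-24 years and HIV-positive status. Neither section asks for an earlier diagnosis, earlier care or an earlier ART prescription. Established infection is explained only as not acute.
- **How they are found.** Teams "aim to screen up to 1500 youths to recruit a cohort of 220 seropositive youths", and "youth in high-risk settings will be asked to complete a brief screening and rapid HIV test". The Abstract names homeless shelters, health clinics and community organisations as venues.
- **Whom the rationale describes.** Description of the Intervention, Level 1, justifies the added component "given that YLH have failed to achieve viral suppression with the existing services available to them".
- **Control rate.** Sample Size Calculations say that, on clinicians' advice, "we expect viral suppression rates to be fairly low in the Enhanced Standard Care condition", with 6% to 20% used. Treatment history is not mentioned.
- **Adjustment.** Data Analyses, Aim 1, brings background characteristics into the multilevel model if they are found to differ between arms.

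**The concern.** A youth diagnosed at screening is unsuppressed because treatment has not begun, so the Level 1 premise is untrue for that participant. The document seems to foresee such entrants. Assessments say "Any study participant who tests positive for HIV or a sexually transmitted infection (STI) will be offered immediate access to treatment", and Retention in Care allows for people who are just starting ART. The Introduction also reports that "Although 41% of YLH know their serostatus, only 62% receive medical care within 12 months of diagnosis", so testing in the community can be expected to find some undiagnosed youth.

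This matters for the comparison because escalation is triggered by non-suppression. In the Abstract, the control arm is standard care plus automated messaging. Level 1 of the stepped arm is in substance the same. A participant who starts first ART and suppresses by the first follow-up stays at Level 1 while suppressed, and so contributes little to the contrast between arms.

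The adjustment rule in Aim 1 does not deal with this. A prognostic factor earns its place in the model because it explains outcome variation, whether or not the arms happen to be unbalanced on it.

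**Working it through.** **1. Reproducing the plan's figure.** Inputs from Sample Size Calculations: 88 evaluable per arm (110 less 20%), 5 time points, compound symmetry, correlation ρ = .1 to .3, two-sided alpha .05, 80% power, control rate 6%-20%.

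Variance factor for a time average: (1 + 4ρ)/5, which is 0.28 at ρ = .1 and 0.44 at ρ = .3. At ρ = .3 the effective size is 88/0.44 = 200 per arm.

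Power = Φ[(d − 1.96·s0)/s1], where s0 = √(2·p̄(1−p̄)/200) and s1 = √((p0(1−p0) + p1(1−p1))/200). For 6% vs 15%: s0 = 0.0307, s1 = 0.0303, (0.09 − 0.0601)/0.0303 = 0.99, power 84%. For 20% vs 33%: also 84%. At ρ = .1 both are 96%.

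Solving for 80% power at ρ = .3 gives 8.5 points (6% control) to 12.3 points (20% control). With a continuity correction it is 9.1 to 12.8, which rounds to the stated 9-13. The calculation is sound for its inputs.

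**2. A higher control rate.** The document gives no rate for newly diagnosed youth. As an assumption, take 30%-44%, the range that the Introduction gives for diagnosed youth. If the whole control arm were at that level, the detectable difference would be 10.7-11.2 points at ρ = .1 and 13.5-14.0 at ρ = .3.

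**3. A mixed cohort.** Assume that 25% are newly diagnosed with control suppression of 30% or 44%, and that the rest are at 6% or 20%. Control rate = 0.25 × (new) + 0.75 × (rest); for example 0.25 × 44% + 0.75 × 6% = 15.5%. If the effect is absent in the newly diagnosed, the arm difference falls to 0.75 × 9 = 6.75 points, or 0.75 × 13 = 9.75 points.

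| Planned pair | New rate | Mixed control rate | No effect in new: power at ρ = .1 / .3 | Same effect in all: power at ρ = .1 / .3 |
|---|---|---|---|---|
| 6% vs 15% | 30% | 12.0% | 65% / 46% | 86% / 68% |
| 6% vs 15% | 44% | 15.5% | 58% / 41% | 81% / 61% |
| 20% vs 33% | 30% | 22.5% | 78% / 59% | 95% / 82% |
| 20% vs 33% | 44% | 26.0% | 75% / 56% | 94% / 79% |

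The ρ = .1 entries in the 6% rows are generous. Two groups at 44% and 6% in these proportions, if stable over time, by themselves induce a within-person correlation of 0.25 × 0.75 × 0.38² / (0.155 × 0.845) = 0.21.

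**The case against.** The strongest reply is that broad eligibility is a legitimate choice. The Objective and the aims concern unsuppressed youth with established infection, not only those in whom treatment has failed. The peer-support and coaching levels address linkage to care as well as adherence. Randomisation keeps the pooled comparison valid, and baseline already covers HIV Treatment Continuum domains. All of this stands. It is why the pooled estimate should stay primary and why the fix is small.

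Four stronger readings are tempting, and the document does not support them.

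- A reader might infer that 6%-20% is a rate for treatment failures and that the sample size is therefore wrong. The section ties the range to clinicians' opinion about the control condition and says nothing of treatment history.
- A reader might take 30%-44% as the rate for new ART starters. It is a proportion of all diagnosed youth, including those already suppressed, who cannot enrol. The Introduction's figures on care entry and retention could equally point to a low rate.
- A reader might use the 41% who know their serostatus to work out that most entrants will be newly diagnosed. That assumes venue screening mirrors all youth with HIV, yet health clinics are among the recruitment sources.
- A reader might quote 41%-59% as the trial's power. That needs no effect in a quarter of the cohort and the top of the correlation range. It also sits uneasily with a 30%-44% suppression rate, at which most of these youth would be unsuppressed at a typical visit and would step up.

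Pre-specified covariates are often left to an analysis plan. Here, however, the article itself states the rule for adjustment, and that rule is conditional on observed imbalance.

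**Conclusion.** The eligibility sections and the Level 1 rationale describe different populations and need reconciling. That rests on the text alone. Dilution of the contrast by youth who suppress on first ART is plausible, but its size cannot be fixed from the document because the newly diagnosed share, their suppression rate and their treatment effect are all unstated. Under a 25% share, power for the planned effects runs from 41% (no effect in that group, ρ = .3) to 95% (same effect, ρ = .1). A shift in control rate alone does little: the detectable difference rises to at most about 14 points, against the stated upper value of 13. The 9%-13% statement is not an error. What is missing is the population to which its control rate applies.

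**What to change.** 1. State whether newly diagnosed or never-treated youth are meant to be included, and make Inclusion and Exclusion Criteria, Recruitment Procedures and the Level 1 rationale agree.
2. Before allocation, record one two-level field: newly diagnosed or never prescribed ART, versus previously prescribed ART. Use self-report, checked against medical records where the participant has consented to access.
3. Enter this field in the primary model as a pre-specified covariate, whatever the observed balance. Report the arm-by-status estimates as supportive, and keep the pooled intent-to-treat estimate primary.
4. In Sample Size Calculations, say which population the 6%-20% describes. Add as a sensitivity figure that control suppression of 30%-44%, labelled as an assumption, gives 10.7-11.2 points at ρ = .1 and 13.5-14.0 at ρ = .3.

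The cost is one field and one model term, with no extra participants or visits. The subgroup estimates will be imprecise. With a 25% newly diagnosed share, about 66 evaluable per arm would remain in the previously treated group (0.75 × 88), and the detectable difference there at 20% control and ρ = .3 is about 14.3 points. Promoting that group to the primary estimate would therefore be a real trade-off and is not recommended here.
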